### Inclusion criteria

Age ≥ 65 years;MMSE score [60] adjusted by age and education ≥ 25/30;Absence of mobility-disability;Absence of need for assistance with Basic Activities of Daily Living (according to the ICFSR International Clinical Practice Guidelines) [52].

### Exclusion criteria

Individuals with specific clinical conditions that may render the intervention unsafe (I.e., severe diseases, unstable health status);Individuals whose adherence to the protocol might be low due to clinical (E.g., cognitive impairment, dialysis) and non-clinical (E.g., plans to relocate out of the study area within the next 3 years) reasons;Individuals unable or unwilling to provide informed consent;Consumption of more than 14 alcoholic drinks per week [one alcoholic drink (equal to 14.0 g of pure alcohol) corresponds to 36 cc of beer (5% alcohol content), 24 cc of malt liquor (7% alcohol content), 15 cc of wine (12% alcohol content), 4.5 cc of distilled spirit or liquor (40% alcohol content)];Difficulty in communicating with the study staff due to speech, language, or (non-corrected) hearing problems;Severe arthritis (E.g., awaiting joint replacement) that would interfere with the ability to participate fully in the study;Lung disease requiring regular use of supplemental oxygen;Severe cardiovascular disease (including New York Heart Association [NYHA] class III or IV, clinically significant congestive heart failure and valvular disease, history of cardiac arrest, presence of an implantable defibrillator or pacemaker, uncontrolled angina);Upper and/or lower extremity amputation;Peripheral arterial disease Lériche-Fontaine 3 or 4;Renal disease requiring dialysis;Current enrolment in another study involving lifestyle, nutrition, or pharmaceutical interventions;Further medical, psychiatric, or behavioural factors that in the judgment of the principal investigator may interfere with the study participation;Further possible illnesses affecting the life expectancy and reducing it to less than 24 months, corresponding to the study's length;Clinical judgment concerning safety or non-compliance, as well as the conditions for which the use of the Sleep Profiler is not recommended (sensitivity of skin or scalp and/or open wounds on the forehead or scalp, allergic reactions to extended exposure to synthetic fabrics (e.g., polyester, rayon), upper respiratory infection or congestion, head circumference less than 21 or greater than 25 inches, forehead vertical measurement (from top of eyebrows to hairline) less than or equal to 2 inches or horizontal measurement (from hairline to hairline) less than or equal to 6 inches).SPPB score < 3 at baseline.

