### Setting and participants

Physically frail sarcopenic [3 ≥ Short Physical Performance Battery (SPPB) score ≤ 8] and healthy active [SPPB score > 8] [51] subjects from 65 years of age and afferent the geriatric and sleep medicine outpatient clinics, not demented and independent in the Basic Activities of Daily Living (ADL), will be categorized on the basis of the reduced sleep quality, self-reported and screened by the Pittsburgh Sleep Quality Index [PSQI (Italian version)] [56, 57] and stratified for the usual level of physical activity assessed by Physical Activity Scale for the Elderly [PASE-I (Italian version)] [58, 59]. The following eligibility criteria are intended to select a population that is at risk of accelerated decline in aging trajectory due to sleep disorders and their related systemic consequences. This age-group shall be selected for the sufficient long-life expectancy: to participate in a longitudinal study that lasts up to 2 years. Targeting this subset of the elderly population we will be able to recruit a non-disabled but at-risk population for a research project employing digital and eHealth technologies for frailty and disability assessment and prevention. Furthermore, we are planning to evaluate the eligibility criteria for those subjects previously enrolled in the SPRINTT clinical trial by the Parma site, completed at the end of 2019 and who have not evolved to a condition of disability or dementia, as well as those older individuals screened in the Trajector-AGE study by the same site, started at the end of 2022 and who were found to be sarcopenic and physically frail.

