### Sample size

An overall sample size of 300 patients was defined according feasibility.

However, according with the primary endpoint and the study design, the statistical power estimation was performed.

More specifically, we simulated the width from the lower limit of 95% confidence intervals for the Ratio Between Two Proportions.

The following parameters and assumptions were included into the equation:overall sample size of 300 patients;assumption of the balanced numbers (1:1) of physically frail sarcopenic [3 ≥ SPPB score ≤ 8] and healthy active elderly [SPPB score > 8] individuals;assumption of the unbalanced numbers (2:1) of individuals with and without sleep disorders at the baseline;expected rate of 9% of SPPB score < 9 at 12 months in healthy active elderly individuals [SPPB score > 8] without sleep disorders [118–123];expected rate of 27% of inability to complete a 400 m walk test in less than 15 min (without sitting, stopping for more than one minute, receiving help, or using a walker) in physically frail sarcopenic elderly individuals [3 ≥ SPPB score ≤ 8] without sleep disorders [18];an overall risk ratio of 1.55 at 12 months for individuals with sleep disorders versus the ones without sleep disorders (pooled expected rate 18%);an alpha error of 5%;

Thus, to reject the null hypothesis the lower limits of the ratio must not be lower than 1.11 (corresponding to a 20% of the lower limit of the differences).

Participants will be enrolled at the Frail elderly lab of the Geriatric Clinic Unit within the Interagency integrated activity department of continuity and multicomplexity of the University Hospital of Parma, by acquisition of informed consent and if, upon the geriatric multidimensional assessment, the eligibility criteria given in this study protocol will be met.

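### The alcohol exclusion defines one drink in two ways that differ about tenfold (14.0 g of alcohol against volumes holding 1.3 to 1.4 g); separately, the SPPB range of the frail stratum is printed with its first sign reversed

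*Protocol article*

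**What the plan says.** **Alcohol.** The Exclusion criteria list "Consumption of more than 14 alcoholic drinks per week" and define the unit in a bracket. The bracket opens with "one alcoholic drink (equal to 14.0 g of pure alcohol) corresponds to 36 cc of beer (5% alcohol content") and goes on with "24 cc of malt liquor (7% alcohol content"), "15 cc of wine (12% alcohol content") and "4.5 cc of distilled spirit or liquor (40% alcohol content").

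**SPPB.** Setting and participants gives the physically frail sarcopenic group as "3 ≥ Short Physical Performance Battery (SPPB) score ≤ 8". Sample size prints the range in the same form twice. The first is in the 1:1 balance assumption, "physically frail sarcopenic [3 ≥ SPPB score ≤ 8] and healthy active elderly [SPPB score > 8] individuals"; the second is in the assumption on the 27% event rate. The Exclusion criteria end with "SPPB score < 3 at baseline". The Comprehensive geriatric assessment section gives the SPPB scale as 0 to 12.

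**Link to the endpoint.** Under Outcomes, the primary endpoint depends on the group. For healthy active participants it is an SPPB score below 9 at 12 months. For physically frail sarcopenic participants it is failure to complete the 400 m walk within 15 minutes.

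**The concern.** Both statements are decision limits rather than background. The first decides who may enter. The second decides which group a participant belongs to, and so which primary endpoint is applied.

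In the alcohol criterion, a drink is defined once by mass and once by volume and strength. If the two do not describe the same quantity, one criterion carries two thresholds, and two people applying it in good faith could reach different decisions on the same participant. The volumes deserve care because reported intake usually arrives as glasses or measures and has to be converted. Alcohol also bears on the exposure: the Background says that it disturbs sleep architecture, sleep duration and circadian timing.

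In the SPPB range, the first inequality sign points the wrong way for a range with 3 at the bottom and 8 at the top. Taken at face value, the printed line does not describe the group that the rest of the article describes.

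**Working it through.** **Alcohol: inputs.** From the Exclusion criteria: 14.0 g per drink; beer 36 cc at 5%; malt liquor 24 cc at 7%; wine 15 cc at 12%; spirits 4.5 cc at 40%; a limit of 14 drinks a week. Ethanol density is not in the article. I assume 0.789 g/cc, and use 1.0 g/cc as an upper bound, which also covers reading the percentages as weight in a drink of about 1 g/cc.

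**Formula.** Grams = volume (cc) × alcohol fraction × density.

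| Drink | Pure alcohol (cc) | Grams at 0.789 g/cc | 14.0 ÷ grams | Grams at 1.0 g/cc | Grams at 0.789 if the volume is read as cl |
|---|---|---|---|---|---|
| Beer | 36 × 0.05 = 1.80 | 1.42 | 9.9 | 1.80 | 14.2 |
| Malt liquor | 24 × 0.07 = 1.68 | 1.33 | 10.6 | 1.68 | 13.3 |
| Wine | 15 × 0.12 = 1.80 | 1.42 | 9.9 | 1.80 | 14.2 |
| Spirits | 4.5 × 0.40 = 1.80 | 1.42 | 9.9 | 1.80 | 14.2 |

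The stated 14.0 g is not reproduced by any of the four drinks. Even at the upper bound the volumes fall short by a factor of 14.0 ÷ 1.80 = 7.8 to 14.0 ÷ 1.68 = 8.3, so no plausible density closes the gap. The last column shows that a single change of unit brings all four close to 14.0 g.

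**Weekly limit.**
- By grams: 14 × 14.0 = 196 g a week.
- By the printed volumes: 14 × 1.42 = 19.9 g for beer, wine or spirits, and 14 × 1.33 = 18.6 g for malt liquor. In wine this is 14 × 15 = 210 cc a week.
- At the upper-bound density: 14 × 1.68 = 23.5 g to 14 × 1.80 = 25.2 g.

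**SPPB: listing the scores 0 to 12.**
- Literal reading of the printed range (3 ≥ score and score ≤ 8): 0, 1, 2, 3. The upper limit of 8 does no work.
- After removing scores below 3, as the Exclusion criteria require: 3 only.
- Healthy active (score > 8): 9 to 12.
- In neither group on the literal reading: 4 to 8.
- With the first sign turned (3 ≤ score ≤ 8): 3 to 8. This meets the exclusion below and the healthy stratum above, with no gap or overlap.

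**Effect on the sample size.** None. Sample size says that the 300 was set by feasibility, and the calculation assumes 1:1 groups with rates of 9% and 27%. Neither the drink volumes nor the sign of the inequality enters it.

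**The case against.** The strongest reply is that both slips can be seen through.

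On alcohol, the operative rule is 14 drinks with a drink defined as 14.0 g, and this alone gives a coherent limit of 196 g a week. The volumes are a conversion aid. A drink of 15 cc of wine or 4.5 cc of spirits is implausible enough that a reader would suspect a unit slip. This stands in part: the gram definition survives the error. It does not dispose of the point, because the wrong equivalents sit inside the eligibility criterion itself.

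On SPPB, the literal reading makes the upper limit of 8 redundant, and the intended range follows from the surrounding text. The exclusion below 3, the healthy stratum above 8 and the healthy-group endpoint of a score below 9 all place the frail group at 3 to 8. This stands, and it makes the SPPB matter a notation error rather than an undefined stratum.

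A reader might infer more than the article supports:
- *That moderate drinkers are being refused and recruitment reduced.* This would need staff or forms to use the printed volumes. The article says only that an eCRF will be prepared, and no screening form is shown.
- *That participants scoring 4 to 8 have no primary endpoint.* Outcomes assigns endpoints by group name, and the group can be recovered as above.
- *That the power calculation is affected.* The printed range only labels a group in the list of assumptions; it is not an input.
- *That volumes of 360, 240, 150 and 45 cc would match 14.0 g exactly.* At the assumed density they give 14.2, 13.3, 14.2 and 14.2 g, so they are approximate equivalents.

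**Conclusion.** The alcohol criterion is wrong as written. It contains two definitions of a drink that differ by a factor of 9.9 to 10.6 (7.8 to 8.3 at the upper-bound density), and so two weekly limits: 196 g by mass and about 19 to 20 g by volume. The only outside input is ethanol density, and the conclusion does not depend on its exact value. That cc was printed for cl is an inference from the near-uniform tenfold shortfall; the article does not say so.

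The SPPB range carries a secondary notation error, a reversed first sign printed three times: once in Setting and participants and twice in Sample size. The rest of the text resolves it to 3 to 8. It merits correction because this stratum decides which primary endpoint applies.

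Neither error alters the sample size or the power figures, and nothing in the article shows that any participant was wrongly refused or wrongly classified.

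**What to change.** 1. In the Exclusion criteria, reconcile the four volumes with the 14.0 g definition. If the printed numbers were meant as centilitres, changing the unit is enough; the text should then call them approximate equivalents, since they give 13.3 to 14.2 g.
2. Check that the screening form and the eCRF do not carry the printed volumes. Only if they do is there reason to look back at participants already screened out on alcohol intake.
3. Turn the first sign of the SPPB range in all three places, so that it agrees with the exclusion below 3 and the healthy stratum above 8 (3 ≤ SPPB ≤ 8).

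The cost is a short erratum and one check of the forms. No recalculation and no change to the design or analysis is needed.

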### Withdrawal criteria

At any time, a participant could stop her/his participation in the study.

The reasons for early study's interruption will be:Occurrence of any event that, according to the investigator, may interfere with the study participation or create an unjustified risk for the participant;Illness or a condition leading to prolonged immobilisation;Major deviation(s) to protocol incompatible with continuation in the study;Any medical event requiring administration of an unauthorised concomitant treatment;Non-medical reason;Lost to follow-up: a patient can be declared by the investigator "lost to follow up", in case the investigator has no news about the participant, in spite of all the efforts to contact him/her, in order to find out the reasons for the interruption and convince him or her to come to the final visit.

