### Study design

The SOMNUS-DARE is prospective cohort study improving both the previous SPRINTT project [18] and the current Trajector-AGE (Clinical Trial Number: NCT06168591; Clinical Trial Registry: ClinicalTrials.gov; Registration Date: December 4th, 2023) study [55] expertise. The exposure is represented by the sleep disorders, and the primary outcome is the physical and functional worsening. The duration of the study and the follow up shall be nearly 24 months, according to the time of enrolment in the study and interim power reassessment. Upon approval by the Ethics Committee, the first 6 months will be dedicated to the team members’ training, the participants' enrolment, and the database setup and logistics arrangement. In order to maximize the statistical power of the analyses, each participant will be insured the same follow-up's length, according to the date of his/her recruitment. Those who will be enrolled at the beginning of the recruitment phase will have the same follow-up duration compared with those who will be included at the end of recruitment. Therefore, a 2-year follow-up will be guaranteed. Participants’ follow-up will take place at 3 time points: baseline, 12 and 24 months, by performing the measurements described below in the specific chapter (Fig. 4). The final 6 months of the study will be devoted to progressively carrying out of all the end-of-study visits and measurements, database cleaning and statistical analysis, as well as to predisposing both submission of papers to international scientific journals and disseminating results in international and national conferences.

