### Outcomes

The primary outcome is the incidence of physical and functional worsening at 12 months (Fig. 7).

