**Fig. 7 Fig7:**
[figure not shown]
SOMNUS-DARE analytic aspects

It will be measured in terms of SPPB score < 9 [51, 52] for healthy active elderly individuals and in terms of inability to complete a 400 m walk test in less than 15 min (without sitting, stopping for more than one minute, receiving help, or using a walker) [53] for physically frail sarcopenic elderly Individuals.

The secondary and exploratory outcomes have already been listed in Table 1.

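### Prolonged immobilisation ends participation although the 12-month primary outcome is loss of physical function, so would-be events can be lost selectively

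*Protocol article*

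**What the plan says.** The study is observational: "The SOMNUS-DARE is prospective cohort study", with sleep disorders as the exposure and assessments at baseline, 12 and 24 months (Study design). The same section promises every participant equal follow-up of two years.

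The Withdrawal criteria open a list with "The reasons for early study's interruption will be". Three of its items matter here:
- "Illness or a condition leading to prolonged immobilisation"
- "Occurrence of any event that, according to the investigator, may interfere with the study participation", which is left to judgement
- "Any medical event requiring administration of an unauthorised concomitant treatment", although the article describes no study treatment and no list of permitted treatments.

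Under Outcomes, "The primary outcome is the incidence of physical and functional worsening at 12 months". For healthy active participants, "It will be measured in terms of SPPB score < 9". For frail sarcopenic participants the event is "inability to complete a 400 m walk test in less than 15 min". The Comprehensive geriatric assessment section classes failure of that walk as mobility disability.

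The article does not say that a participant withdrawn under these items is still assessed or is counted as an event. Efforts to secure a final visit are mentioned only in the lost-to-follow-up item.

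**The concern.** A participant who is still immobilised at month 12 would meet either component of the primary outcome. The withdrawal list therefore ends participation for a state that overlaps with the endpoint, before the visit at which the endpoint is measured. The discretionary item widens this route, because a decline in function is an obvious example of an event that interferes with participation.

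If these people leave without an outcome, they drop out of both numerator and denominator, and they do so because of how they are faring. Incidence, the quantity named as the primary outcome, comes out too low. The risk ratio is distorted as well unless the removal shares in the two sleep groups happen to balance. An analysis plan can decide how to classify withdrawn people, but it cannot supply 12- or 24-month assessments that were never made.

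**Working it through.** **Inputs (Sample size section).** There are 300 participants, two with sleep disorders for each one without: 200 exposed and 100 unexposed. Expected rates without sleep disorders are 9% (healthy active) and 27% (frail sarcopenic), with the two physical strata in equal numbers. The risk ratio is 1.55.

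**The plan's own figures.** (9% + 27%)/2 = 18%, which reproduces the stated pooled rate. I read it as the unexposed risk, since both components are for people without sleep disorders. Exposed risk: 1.55 × 18% = 27.9%. Expected events: 100 × 0.18 + 200 × 0.279 = 18 + 55.8 = 73.8, or 24.6% of 300. The plan's lower limit of 1.11 is not used in this check.

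**Withdrawal rate.** The article gives none; the Discussion only names attrition as a challenge. The shares below are assumptions.

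**Formula.** Let a share f of would-be events be withdrawn before month 12 and dropped, with no non-events dropped. Then:
- observed risk q = p(1 − f)/(1 − pf)
- observed odds q/(1 − q) = (1 − f) × p/(1 − p), so the odds ratio is multiplied by (1 − f1)/(1 − f0), where 1 is exposed and 0 unexposed.

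Worked example, f1 = 20%, f0 = 10%:
- exposed: 0.279 × 0.80/(1 − 0.0558) = 0.2232/0.9442 = 23.6%
- unexposed: 0.18 × 0.90/(1 − 0.018) = 0.162/0.982 = 16.5%
- risk ratio = 1.43
- events lost = 200 × 0.279 × 0.20 + 100 × 0.18 × 0.10 = 11.2 + 1.8 = 13.0
- overall incidence = (73.8 − 13.0)/(300 − 13.0) = 21.2%, against 24.6%.

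| Share lost, unexposed / exposed (assumed) | Risk unexposed | Risk exposed | Risk ratio | Odds ratio | Events lost |
|---|---|---|---|---|---|
| 0 / 0 | 18.0% | 27.9% | 1.55 | 1.76 | 0 |
| 2% / 5% | 17.7% | 26.9% | 1.52 | 1.71 | 3.2 |
| 10% / 10% | 16.5% | 25.8% | 1.57 | 1.76 | 7.4 |
| 20% / 20% | 14.9% | 23.6% | 1.58 | 1.76 | 14.8 |
| 10% / 20% | 16.5% | 23.6% | 1.43 | 1.57 | 13.0 |
| 10% / 30% | 16.5% | 21.3% | 1.29 | 1.37 | 18.5 |
| 20% / 10% | 14.9% | 25.8% | 1.73 | 1.98 | 9.2 |

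Both risks fall in every row with any loss. The risk ratio falls if exposed events are lost clearly more often, rises slightly under equal loss, and rises more if unexposed events are lost more often. It stays at 1.55 only at a chance balance, for example 10% unexposed with 11.2% exposed.

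**The case against.** Several points on the other side have force.

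- **A biased risk ratio is not demonstrated.** A reader might infer that the rule pulls the risk ratio towards 1. The document does not support that. It gives no withdrawal rate, does not say that removal differs by sleep status, and does not say outright that withdrawn people leave the analysis. Equal loss barely moves the ratio.
- **Modelling is not always powerless.** A reader might also infer that no analysis of those who remain can help. If removal depends on the outcome alone, the odds ratio is preserved, and the Statistical methods section plans logistic regression. Risks and the risk ratio are still affected, and under differential removal so is the odds ratio.
- **The overlap is partial.** Immobilisation from illness is more severe than many primary events. A healthy active participant who enters with an SPPB score of 9 becomes an event by losing one point. Many events will occur in people who walk into the clinic, and some immobilisation will resolve before month 12. Shares of 20% to 30% may be far too high; at 2% / 5% the risk ratio is 1.52.
- **Part is already covered.** A participant who attends but cannot do an SPPB component scores 0 on it, and one who cannot finish the walk is classed as mobility disabled. Only those withdrawn before the visit are at issue.
- **Some things may need stopping.** It is tempting to say that an observational study has nothing to stop. This one includes contrast MRI, amyloid PET and repeated blood sampling, and the first withdrawal item also covers unjustified risk to the participant.

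These points limit the size and certainty of the effect on the risk ratio. They do not close the gap: the rule ends participation for a state that overlaps with the endpoint, and nothing stated keeps these people under ascertainment. Because the protocol itself fixes who leaves follow-up, the matter cannot be left to the analysis plan.

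**Conclusion.** The concern holds in this form: followed as written, the Withdrawal criteria remove would-be primary events selectively, and they conflict with the outcome definition and with the promise of equal two-year follow-up. Incidence is understated whenever withdrawn participants have no outcome assigned and would-be events are removed more often than non-events. The effect on the risk ratio is undetermined in direction and size. The figures of 1.43 (20% exposed, 10% unexposed) and 1.58 (20% in both), against 1.55 planned, only illustrate assumed shares, and smaller shares give smaller shifts.

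**What to change.** Reconcile the Withdrawal criteria with the Outcomes section:

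1. Separate stopping study procedures, which may stay at the investigator's discretion for safety, from ending outcome ascertainment. Only withdrawal of consent, death or true loss to contact should end ascertainment.
2. Continue to ascertain mobility status at 12 and 24 months in participants who become immobilised.
3. Classify as having the primary event those who at 12 months are still immobilised and cannot perform the SPPB or the 400 m walk because of lasting loss of mobility. Counting every health-related non-attempt would go too far: an acute, reversible illness at month 12 would then be recorded as functional worsening.
4. Record the reason for not attempting the test in the eCRF.
5. Run sensitivity analyses for acute reversible immobilisation and for death before 12 months.
6. Reconcile the item on unauthorised treatment with the cohort design, since the article does not define the term.

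The cost is a short amendment, one eCRF reason code and some remote or home ascertainment of mobility status. The downside is some misclassification of reversible cases, which the sensitivity analysis will show. The change should precede the 12-month visits, because follow-up that was not done cannot be rebuilt.
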